### Outcome measures

#### Hamilton Depression Scale-17

Hamilton Depression Scale-17 (HAMD-17) is recommended as the primary endpoint for depression in clinical trials (33). HAMD-17 will evaluate changes in depression levels from baseline to the end of the follow-up.

#### MDS Unified-Parkinson Disease Rating Scale-III

The MDS Unified-Parkinson Disease Rating Scale-III (UPDRS-III), revised by the International Parkinson and Movement Disorder Society, is the most commonly used evaluation scale for PD in clinical and scientific research settings (34, 35). The UPDRS-III will evaluate changes in motor symptoms by counting tremor and non-tremor symptoms of PD.

#### Quick Inventory of Depressive Symptomatology-Self Report

The Quick Inventory of Depressive Symptomatology-Self Report (QIDS-SR) scale is a simple and feasible depression screening scale. It exhibits high sensitivity, specificity, and clinical practicality (36, 37). The QIDS-SR will assist in evaluating changes in depression levels from baseline to the conclusion of the follow-up period.

#### Parkinson’s Disease Patient Quality of Life Questionnaire-39 (PDQ-39)

The PDQ-39 can assess the QoL for Chinese patients with PD, regardless of whether they have cognitive impairment (38, 39). The PDQ-39 will be used to evaluate changes in QoL from the baseline to the end of the follow-up.

#### MRI data

Patients will undergo cranial magnetic resonance imaging at baseline and after treatment. The MRI scan will be conducted using a 3.0 Tesla superconducting magnet (Siemens MAGNETOM Skyra 3.0 T) at the Beijing Hospital of Traditional Chinese Medicine Affiliated with Capital Medical University. The parameters of the sequences used are as follows: Slices = 300, TR = 2,000 ms, TE = 30 ms, Slice thickness = 4.0 mm, FoV read = 200 × 200 mm^2^, Flip angle = 90°, Voxel size = 3.1 × 3.1 × 4.0 mm, Base resolution = 64, Phase resolution = 100%, TA = 10.06 min.

##### Primary indicator

The response rate (The response rate, defined as the proportion of total scores that decreased by at least 50% compared with baseline statistics) of HAMD-17 (at week 12).

##### Secondary indicator

The change from baseline in resting-state fMRI (at week 12). The response rate of HAMD-17 (at weeks 24, and 48). The changes from baseline in UPDRS-III and PDQ-39 (at weeks 12, 24, and 48). The response rate of QIDS-SR, and the change from baseline in PDQ-39 (at weeks 12, 24, and 48). The proportion of patients with progression≥0.5 grades compared to the baseline of H–Y staging (at week 48).

### Safety assessments

Any adverse effects (AEs) happening throughout the study period, whether reported spontaneously by the participants or observed by the researchers, will be recorded and categorized as needling-related AEs. Common adverse events associated with acupuncture include persistent post-needling pain, dizziness, subcutaneous hematoma, infection, etc. Serious adverse events will be reported and handled according to relevant regulations within 24 h.

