**Methods and analysis:**

In this randomized, single-blinded, and placebo-controlled study, a total of 88 patients with depression in Parkinson’s disease (DPD) will be randomly allocated to either an acupuncture group or a control group in parallel in a 1:1 allocation ratio. Each group will receive 30 min acupuncture treatments or sham acupuncture treatments, 3 times a week, for 12 weeks, followed by a 36-week follow-up period. The primary outcome is the response rate of the Hamilton Depression Rating Scale-17 at 12 weeks. Data will be collected at baseline, at the end of the 12-week treatment period, and during the 12-week and 36-week follow-up.

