### Sample size calculation

In this study, the sample size was calculated using G*Power 3.1 software, and the HAMD-17 response rate was selected as the primary outcome. We also designed a pre-trial. The results of our pre-trial study showed that the response rate of DPD in the acupuncture group was 92%. When conducting a one-sided significance test, the ratio of the two groups is 1:1, and the setting of *α* = 0.05, *β* = 0.80. The calculated preliminary sample size is 78 patients. Considering a dropout rate of 10%, and a corrected sample size of 87 cases. Ultimately, 88 patients will be included, with 44 patients in each group.

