### Statistical analysis

#### Clinical data analysis

Statistical analysis will be conducted utilizing SPSS 20.0 (IBM Corporation, Armonk, NY, United States), a software package to analyze statistical data. Statistical significance was determined at the 0.05 level (two-tailed). The intention-to-treat (ITT) analysis will be employed as the primary analysis for all patients, and missing data were filled in using the last observation carried forward (LOCF). A supplementary analysis will be conducted using the adherence protocol analysis (PP).

The categorical data will be described using frequencies and percentages. The proportion of patients with progression ≥0.5 grades compared to the baseline of H–Y staging, and adverse events were analyzed using the chi-squared test. The initial step in the analysis of continuous data is to assess their normality. The data are described using mean ± standard deviation or median (interquartile range). Within-group comparisons are conducted using either paired *t*-tests or Wilcoxon signed-rank tests, while between-group comparisons are carried out using independent samples *t*-tests or Mann–Whitney *U* tests. HAMD-17, QIDS-SR, UPDRS-III, and PDQ-39 were analyzed using either repeated-measures ANOVA or a generalized linear mixed model based on repeated measurements.

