## Discussion

The principal objectives of this study are to evaluate the clinical efficacy and safety of acupuncture in the treatment of DPD and to investigate its mechanisms of neural regulation. The results of these studies will contribute to the establishment of a therapeutic program for effective and safe acupuncture intervention in DPD.

Depression is a common occurrence in early PD and persists throughout all stages, significantly impacting patients’ quality of life (40). The development of new therapeutic approaches to treat DPD is essential to improve the quality of life of DPD patients (41). This study was conducted following the academic experience of a renowned Chinese physician, [name], in treating PD. This study was a randomized, evaluator-blinded, sham acupuncture placebo-controlled trial to assess the efficacy and safety of acupuncture intervention for early mild-to-moderate DPD.

The present study has several innovative strengths. First, to the best of our knowledge, this study represents the first randomized controlled trial of acupuncture treatment for patients with early PD (H–Y staging ≤ grade 2.5) and mild-to-moderate depression, based on the internationally recognized Hoehn–Yahr staging criteria for PD. This study addresses the shortcomings of previous acupuncture research by separating DPD patients based on the severity of their condition. It investigates the potential benefits of early acupuncture intervention in DPD to determine if it can effectively delay the progression of PD during mid to long-term follow-up.

Secondly, this study selected scale and questionnaires and a combination of brain fMRI technology as the efficacy evaluation indicators. This study included fMRI data collection to explore the objective mechanism of acupuncture for early Parkinson’s disease with mild to moderate depression. Recent neuroimaging studies have begun to reveal the central mechanism of DPD (42–44), but the mechanism of acupuncture interventions to regulate the central nervous system remains is still unclear. The present study provides a foundation for future research on the central mechanisms of acupuncture treatment.

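### The safety rule labels every adverse event over 48 weeks as needling-related, which overstates that rate in both arms and dilutes the needling-specific comparison

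*Protocol article*

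**What the plan says.** All references are to the protocol article.

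- **Safety assessments.** The scope is "Any adverse effects (AEs) happening throughout the study period", and these events, "whether reported spontaneously by the participants or observed by the researchers, will be recorded and categorized as needling-related AEs". That is the only category named. The section goes on to list common acupuncture events (lasting pain after needling, dizziness, hematoma, infection) and to require serious events to be reported within 24 hours. It does not say that anyone judges cause.
- **Abstract, Methods and analysis.** Treatment is given "3 times a week, for 12 weeks, followed by a 36-week follow-up period", so the study period is 12 + 36 = 48 weeks. Table 1 agrees, with the last assessment at week 48.
- **Clinical data analysis.** On the comparison between arms, "adverse events were analyzed using the chi-squared test". The significance level is 0.05, two-sided.
- **Sample size calculation.** "Ultimately, 88 patients will be included, with 44 patients in each group".
- **Discussion.** "The principal objectives of this study are to evaluate the clinical efficacy and safety of acupuncture in the treatment of DPD".

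**The concern.** The rule fixes three things: any event, the whole study, one label. Taken at its word, a drug side effect or an intercurrent illness in week 40, some 28 weeks after the last needle, is a needling-related event.

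Such background events are foreseeable here. The inclusion criteria admit patients aged 50 to 75 on a fixed anti-Parkinson drug regimen. The Introduction says that dopamine agonists can cause impulse-control and sleep problems. The Discussion says that medication use could not be controlled. Some listed acupuncture events, such as dizziness and infection, also arise without needling and cannot be told apart by type alone.

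Two results are at stake. The first is the needling-related rate in each arm, which readers will take as the harm profile of the treatment. The second is the contrast between acupuncture and sham on needling harm. Sham needles also enter the skin (2 to 4 mm, Interventions section), so both arms can have true needling events and the contrast is a real question. The article calls safety a principal objective.

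**Working it through.** **Is there a figure to reproduce?** No. The article states no adverse event rate and no power for safety. The wording can be checked directly; the size of the effect can only be illustrated.

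**Step 1: the wording.** Safety assessments supplies the scope (any event), the window (study period) and the category (needling-related). The Abstract and Table 1 make the window 48 weeks, and needling occupies 12 of them. The remaining 36 weeks are 36/48 = 75% of the window. No other section adds an attribution step or a second category.

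**Step 2: effect on the reported rate.** Let r be the probability that a patient has a true needling-related event and b the probability of a background event, taken as independent and with b equal in both arms. Under the rule, the proportion labelled needling-related is

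p = 1 − (1 − r)(1 − b).

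This exceeds r whenever b > 0 and r < 1, so the rate is too high in both arms. For r = 20% and b = 10%: p = 1 − 0.80 × 0.90 = 28%. For r = 5% and b = 10%: p = 1 − 0.95 × 0.90 = 14.5%.

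**Step 3: effect on the contrast.** With rates r1 and r2 in the two arms,

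p1 − p2 = (1 − b)(r1 − r2).

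The difference shrinks by the factor (1 − b). It does not vanish.

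**Step 4: power.** Inputs from the article: 44 per arm, two-sided 0.05, chi-squared test. Assumed inputs: all values of r1, r2 and b. Power is by exact enumeration of the chi-squared test without continuity correction, over all pairs of binomial counts. The row with b = 0 is the analysis of needling-related events alone, if they were classified without error.

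| True needling rates | Background b | Labelled rates | Difference (points) | Risk ratio | Power |
|---|---|---|---|---|---|
| 20% vs 5% | 0 | 20% vs 5% | 15 | 4.0 | 62% |
| | 5% | 24% vs 9.8% | 14.3 | 2.5 | 45% |
| | 10% | 28% vs 14.5% | 13.5 | 1.9 | 35% |
| | 20% | 36% vs 24% | 12 | 1.5 | 24% |
| | 40% | 52% vs 43% | 9 | 1.2 | 12% |
| 40% vs 10% | 0 | 40% vs 10% | 30 | 4.0 | 93% |
| | 5% | 43% vs 14.5% | 28.5 | 3.0 | 87% |
| | 10% | 46% vs 19% | 27 | 2.4 | 80% |
| | 20% | 52% vs 28% | 24 | 1.9 | 65% |
| | 40% | 64% vs 46% | 18 | 1.4 | 39% |

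**Step 5: the all-cause comparison.** A label given to every event in both arms changes no count. The all-cause table is the same with or without it.

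**The case against.** The strongest reply has four parts.

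1. *No difference is hidden.* A reader might infer that the rule conceals any true safety difference between the arms. The article does not support that. Every event is recorded, the arms are randomised, and adverse events are compared by a chi-squared test, so an all-cause difference stays visible. This part stands. What is lost is the separate needling-specific rate, and power for that contrast.

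2. *The pooled test is partly inferred.* The analysis section does not say that only one table of any event is tested, and nothing rules out tables by event type. Pain after needling and hematoma could be recognised by type whatever the label. This stands in part: it limits the dilution, but does not remove it for dizziness or infection.

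3. *It may be a drafting slip.* The sentence may be shortened from wording such as needling-related or not, and an adverse event form, which is not shown, may carry a relatedness field. That is possible, so the article cannot prove that no attribution is made in practice. But the article is not silent here. It states a rule, and the rule as printed is wrong. If it is a slip, it still needs correcting.

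4. *The size rests on assumptions, and the trial is not sized for safety.* Both are true. The loss runs from modest (93% to 87%) to large (62% to 12%), depending on rates that the article does not give. The low power values break no design claim.

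**Conclusion.** The rule is wrong as written. Applied literally, it overstates the needling-related adverse event rate in both arms; this needs only that some background events occur over 48 weeks. It also dilutes the needling-specific contrast by the factor (1 − background rate). The power losses in the table assume equal and independent background rates, one yes/no result per patient, all 44 per arm analysed, and error-free classification in the comparison row. They show a range and do not predict what this trial will see.

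Severity is moderate. The primary outcome (HAMD-17 response at week 12), the listed secondary indicators, the randomisation and the reporting of serious events are untouched. The point matters because safety is named as a principal objective, and because a judgement of cause is best made when the event is recorded.

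**What to change.** Reword the sentence in Safety assessments so that all adverse events in the study period are recorded and each is classified as needling-related or not needling-related. Existing study staff can make the classification, blind to arm where possible. Report all-cause and needling-related events separately by arm, and distinguish the 12-week treatment period from the 36-week follow-up. Reclassify events already recorded in the same way; the Progress of research section says that recruitment and treatment are under way, so sooner means fewer to revisit.

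The cost is one sentence in the protocol, one field on the adverse event form if it is not already there, and a review of past events. No treatment, visit or sample size changes.

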### Data management and quality control

At baseline, information on the patient’s age, gender, occupation, education level, dominant hand, medical history, etc. We will arrange for patients who meet the inclusion criteria to undergo questionnaire evaluation in a quiet room with no unrelated personnel, followed by an fMRI examination. All fMRI will be conducted using the same 3.0 T MRI machine.

The case report form (CRF) that has been approved on ethical grounds will be used to collect clinical data on each enrolled patient. The data from the paper CRF forms will be entered into a Microsoft Excel spreadsheet independently by two researcher assistants. A comparison of the data entry results between the two research assistants will be conducted to identify any inconsistencies. Any discrepancies in the electronic data will be validated by a third independent research assistant who will review the paper data. The electronic data will be analyzed using SPSS 20.0 software (IBM Corporation, Armonk, NY, United States).

### Statistical analysis

#### Clinical data analysis

Statistical analysis will be conducted utilizing SPSS 20.0 (IBM Corporation, Armonk, NY, United States), a software package to analyze statistical data. Statistical significance was determined at the 0.05 level (two-tailed). The intention-to-treat (ITT) analysis will be employed as the primary analysis for all patients, and missing data were filled in using the last observation carried forward (LOCF). A supplementary analysis will be conducted using the adherence protocol analysis (PP).

The categorical data will be described using frequencies and percentages. The proportion of patients with progression ≥0.5 grades compared to the baseline of H–Y staging, and adverse events were analyzed using the chi-squared test. The initial step in the analysis of continuous data is to assess their normality. The data are described using mean ± standard deviation or median (interquartile range). Within-group comparisons are conducted using either paired *t*-tests or Wilcoxon signed-rank tests, while between-group comparisons are carried out using independent samples *t*-tests or Mann–Whitney *U* tests. HAMD-17, QIDS-SR, UPDRS-III, and PDQ-39 were analyzed using either repeated-measures ANOVA or a generalized linear mixed model based on repeated measurements.

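### LOCF is fixed for every outcome: a missing week-48 Hoehn–Yahr stage becomes no progression, and an end-of-treatment response can be counted as sustained; the week-12 primary endpoint is not affected in this way

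*Protocol article*

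**What the plan says.** Under Clinical data analysis, the protocol article states that "The intention-to-treat (ITT) analysis will be employed as the primary analysis for all patients", and in the same sentence that "missing data were filled in using the last observation carried forward (LOCF"). No outcome or visit is excepted. The only other analysis named is per protocol: "A supplementary analysis will be conducted using the adherence protocol analysis (PP"). That analysis changes the population; it does not test the missing-data assumption.

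The abstract gives the visits: "Data will be collected at baseline, at the end of the 12-week treatment period, and during the 12-week and 36-week follow-up". Table 1 places them at weeks 0, 12, 24 and 48. HAMD-17, QIDS-SR, UPDRS-III and PDQ-39 are scheduled at all four, H–Y at baseline and week 48 only.

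The late secondary endpoints include "The response rate of HAMD-17 (at weeks 24, and 48"), QIDS-SR response at weeks 12, 24 and 48, and "The proportion of patients with progression≥0.5 grades compared to the baseline of H–Y staging (at week 48"). H–Y progression goes to a chi-squared test. The four scales go to repeated-measures ANOVA or a generalized linear mixed model, and the article does not say whether that model uses observed or filled data.

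**The concern.** LOCF assumes that a patient stays where last seen. With so few visits the last observation may be far away: 48 weeks for H–Y, and up to 36 weeks for the scales at week 48 in a patient last seen at week 12.

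Two binary endpoints suffer most.

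- **H–Y progression.** Baseline is the only value that can be carried, so the change is zero by construction and loss to follow-up is scored as a good outcome. The Discussion asks whether early acupuncture delays progression of Parkinson's disease over mid- to long-term follow-up, and this endpoint speaks to that question.
- **HAMD-17 and QIDS-SR response at weeks 24 and 48.** Treatment stops at week 12. A responder who then leaves is counted as a responder later, so the arm with more week-12 responders gains apparent durability even if the true late rates are equal.

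UPDRS-III and PDQ-39 would likewise be held at earlier values in a progressive disease, if the repeated-measures analysis is run on filled data.

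**Working it through.** **The plan's own figure.** Under Sample size calculation, 78 patients with 10% dropout gives 78/(1 − 0.10) = 86.7, rounded up to 87, then 88 (44 per arm). The figure reproduces. The 10% is the only statement about expected loss, and it is not tied to a visit.

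**Carry-forward spans, from Table 1.** H–Y: 48 − 0 = 48 weeks. Scales at week 48: 48 − 12 = 36 weeks if weeks 24 and 48 are both missing; 48 − 24 = 24 weeks if only week 48 is missing.

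**Primary endpoint.** The only HAMD-17 value before week 12 is baseline. Carrying it forward gives a 0% fall, which is below the 50% needed for response. LOCF therefore gives the same result as counting missing patients as non-responders.

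**H–Y progression.** With true progression *p* and missing fraction *d*, and missingness unrelated to outcome, LOCF reports *p*(1 − *d*). Assume *p* = 25% in both arms (the article gives no rate):

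| Missing, acupuncture/control | LOCF reports |
|---|---|
| 10%/10% | 0.25 × 0.90 = 22.5% vs 22.5% |
| 15%/5% | 0.25 × 0.85 = 21.3% vs 0.25 × 0.95 = 23.8% |
| 25%/5% | 0.25 × 0.75 = 18.8% vs 0.25 × 0.95 = 23.8% |

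In the last row the two-sided chi-squared test at 44 per arm rejects in 9.3% of trials, against 5.3% with nothing missing. Equal loss creates no false difference but shrinks a real one: assumed true rates of 15% vs 30% become 13.5% vs 27% at 10% missing, so 15 points become 13.5.

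**HAMD-17 response at week 48.** For patients missing both late visits, the LOCF rate is (1 − *d*) × *p*48 + *d* × *p*12. Inputs: *p*12 = 92% for acupuncture (the pilot rate in the sample size section); 70% for control (assumed, because no control rate is given); *p*48 = 45% in both arms (assumed), so there is no true late difference. The test is taken as a two-sided 5% chi-squared test at 44 per arm, with rejection probabilities exact from the binomial.

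| Missing, acupuncture/control | LOCF reports | False-positive rate |
|---|---|---|
| none | 45.0% vs 45.0% | 4.7% |
| 10%/10% | 49.7% vs 47.5% | 4.9% |
| 20%/10% | 54.4% vs 47.5% | 9.0% |
| 20%/20% | 54.4% vs 50.0% | 6.3% |
| 30%/20% | 59.1% vs 50.0% | 13.0% |
| 20%/30% | 54.4% vs 52.5% | 4.9% |

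For example, at 30%/20%: 0.70 × 0.45 + 0.30 × 0.92 = 59.1%, and 0.80 × 0.45 + 0.20 × 0.70 = 50.0%.

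**Non-response as the alternative.** At 30%/20% missing, counting missing patients as non-responders gives 0.70 × 0.45 = 31.5% vs 0.80 × 0.45 = 36.0%, a false difference the other way, with 7.8% rejection. It is no neutral substitute for LOCF at the late visits.

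**The case against.** Four arguments on the other side carry weight.

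1. **The primary endpoint.** A reader might infer that LOCF biases the main result of the trial. The documents do not support that: at week 12 it equals non-response, a usual convention for a responder endpoint. The distortion falls on secondary endpoints. This stands.
2. **The planned dropout.** At 10% in each arm there is almost no inflation: 4.9% for late response, and no false difference for H–Y. The larger figures need heavier loss, and mostly loss that is unequal in an unfavourable direction. Nothing in the article predicts 30%/20% or 25%/5%. This also stands, with one qualification: the 10% is a sample-size allowance with no visit attached, and loss by week 48, 36 weeks after treatment ends, may exceed it.
3. **The week-24 visit.** A reader might infer that every week-12 responder missing at week 48 becomes a week-48 responder. That happens only if week 24 is missing too; otherwise the week-24 value is carried. The table above assumes that both are missing, so it is the upper end for a given missing fraction.
4. **The mixed model, and a separate analysis plan.** The article allows a mixed model for the four scales, and a fuller plan could fit it to observed data. So it cannot be said outright that UPDRS-III and PDQ-39 scores will be frozen. But the mixed model is only one of two options, LOCF is stated without exception, and H–Y lies outside that list. LOCF is a rule that the article states, not a detail left for later.

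**Conclusion.** The concern holds for the late secondary endpoints. That a missing week-48 H–Y stage becomes no progression follows directly from the schedule and the stated rule, and needs no assumption. The same is true of a carried response being counted as sustained in patients who do not return after week 12.

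The numerical effect does rest on assumptions: the control response rate, the true week-48 response and progression rates, dropout by arm, missingness unrelated to outcome, and both late visits missing. Under them the effect is negligible at the planned 10%/10%. The false-positive rate for late response rises to 9.0% at 20%/10% and 13.0% at 30%/20%, and H–Y shows a false gap of 5 points at 25%/5%. The direction depends on which arm loses more patients, so one cannot say in advance that LOCF favours acupuncture on progression. This is a point that should be fixed; it does not threaten the primary analysis.

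**What to change.** Remove LOCF from Clinical data analysis and replace it as follows.

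- **Week-12 HAMD-17 response (primary):** state that a missing value counts as non-response. The result is the same as under the present rule.
- **HAMD-17, QIDS-SR, UPDRS-III and PDQ-39 scores:** choose the mixed model already named, and state that it is fitted to observed data without filling.
- **HAMD-17 and QIDS-SR response at weeks 24 and 48, and H–Y progression at week 48:** use multiple imputation by arm, with baseline and all observed visits as predictors. Report non-response (for response) and a worst-case assignment (for H–Y) as sensitivity analyses.
- **Reporting:** give the number missing by arm at each visit.

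The cost is wording, a little more programming and slightly wider intervals. Visits, sample size and treatment do not change. The article says that recruitment is under way, so the change should be dated and made before any unblinded analysis.

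### Safety is a stated principal objective, but the only inference planned for adverse events is a chi-squared difference test with 44 per arm, which cannot support a safety statement

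*Protocol article*

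**What the plan says.** The Discussion sets the aim: "The principal objectives of this study are to evaluate the clinical efficacy and safety of acupuncture in the treatment of DPD", together with the neural mechanism. It expects the results to contribute to "the establishment of a therapeutic program for effective and safe acupuncture intervention in DPD".

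Safety assessments provides for adverse events to be recorded throughout the study, whether patients report them or researchers observe them, and for serious events to be reported within 24 hours. It lists common event types but gives no expected rates.

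Clinical data analysis states two things that bear on these events. First, "The categorical data will be described using frequencies and percentages". Second, "adverse events were analyzed using the chi-squared test". The significance level in the same section is 0.05, two-sided. The article does not say whether the chi-squared test is continuity-corrected, and it states no interval, margin or upper limit for adverse events.

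Sample size calculation rests on the HAMD-17 response rate only and ends with: "Ultimately, 88 patients will be included, with 44 patients in each group".

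Interventions and Table 3 describe a control arm that is also penetrated: 0.18 mm needles at five sham sites, 2–4 mm deep, retained for 30 minutes.

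**The concern.** A test of difference asks whether the data contradict equal event rates. A safety objective asks a different question: how large an excess, or how high an absolute rate, can be ruled out. When events are few and arms are small, the test often fails to reject even if a real excess exists, and the p-value alone does not tell the reader how large that excess could be.

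Two features make this sharper here. The sample size was set for a different endpoint, so nothing ensures useful precision for adverse events. The comparator also produces needling events, so similarity to it says little about the absolute risk of the real treatment.

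At stake is the wording of the final report. A statement that adverse events did not differ significantly could be taken as support for the safe programme that the Discussion looks forward to, when the design cannot supply that support.

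**Working it through.** **Inputs from the article.** 44 per arm, 1:1 allocation, 10% dropout (Sample size calculation); chi-squared test, two-sided 0.05 (Clinical data analysis). **Inputs assumed.** All adverse event rates, shown over a range because the article gives none.

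**The plan's own figure.** The starting figure of 78 cannot be recomputed because no control response rate is given. The dropout step does reproduce: 78 / 0.90 = 86.7, rounded up to 87, then 88 for equal arms, or 44 each. The article states no power or precision for adverse events, so there is no safety figure to reproduce.

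**Power of the stated test.** For a control events and b acupuncture events among n = 44 per arm, X² = 2n[a(n − b) − b(n − a)]² / [(a + b)(2n − a − b)n²], with rejection when X² ≥ 3.841. Power is the sum of Bin(a; 44, p₁) × Bin(b; 44, p₂) over all pairs that reject.

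| Assumed rates (control v acupuncture) | Power, uncorrected | Missed |
|---|---|---|
| 5% v 10% | 16% | 84% |
| 5% v 15% | 38% | 62% |
| 5% v 20% | 62% | 38% |
| 5% v 25% | 80% | 20% |
| 10% v 20% | 27% | 73% |
| 10% v 25% | 48% | 52% |
| 10% v 30% | 68% | 32% |
| 20% v 40% | 55% | 45% |

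The miss rate depends on the base rate as well as on the size of the excess. A 20-point excess has 80% power from a 5% base and 55% from a 20% base.

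**Sensitivity to the form of the test.** At 5% v 15% the pooled rate is 10%, so the expected count is 44 × 0.10 = 4.4 events per arm, below the usual threshold of 5 for the chi-squared approximation. With the continuity correction, power is 19.5% (missed 80%). With Fisher's exact test it is 22.0% (missed 78%). The uncorrected figures are therefore the favourable ones.

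**Sensitivity to dropout.** With 39 per arm, the 5% v 15% case has 34% power (missed 66%).

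**What a non-significant result could hide.** Suppose 6/44 in the acupuncture arm and 2/44 in the control arm have an event.
- X² = 88 × (6 × 42 − 2 × 38)² / (8 × 80 × 44 × 44) = 88 × 176² / 1,239,040 = 2.20, so p = 0.14.
- Observed risks are 13.6% and 4.5%, a difference of 9.1 points. The Wilson intervals are 6.4% to 26.7% and 1.3% to 15.1%.
- Newcombe lower limit: 9.1 − √[(13.6 − 6.4)² + (15.1 − 4.5)²] = −3.7 points.
- Newcombe upper limit: 9.1 + √[(26.7 − 13.6)² + (4.5 − 1.3)²] = +22.6 points.

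The test is non-significant, yet an excess of more than 20 points is not excluded.

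**Absolute risk.** With no events in 44 patients, the upper end of the exact two-sided 95% interval is 1 − 0.025^(1/44) = 8.0%.

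**The case against.** The strongest reply is that the article never states a decision rule for safety. A reader might infer that p > 0.05 is the trial's route to calling acupuncture safe, but no section says so. The Discussion speaks of contributing to a programme, not of demonstrating safety, and Study design describes the aim as effect and neural mechanism without naming safety. This stands. The point is about a method that does not answer the stated objective, not about a false claim or an internal contradiction.

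It is also fair that counts and percentages are already planned, that trials are seldom powered for safety, and that further safety tables may sit in an analysis plan that is not shown. The absence of those tables is therefore not the complaint. What remains is that the article does fix an inferential method for adverse events, and the one it fixes cannot bear on the objective named in its Discussion.

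Finally, the event rates are the reviewer's. A reader might infer that the test will most likely be non-significant whatever the harm. The table does not support that: 5% v 20%, 10% v 30% and 20% v 40% are each more likely to be detected than missed.

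**Conclusion.** The point holds as a matter of analysis choice, at minor to moderate severity. Safety is a named principal objective, and the stated inference is a difference test in 44 per arm, sized on HAMD-17 response and made against a needled control. Over the assumed rates shown, the uncorrected test misses between 20% and 84% of real excesses; 5% v 15% is missed 62% of the time, or about 80% with continuity correction. These percentages rest on the assumed rates and on all 44 patients per arm being analysed. The conclusion that non-significance cannot establish safety does not depend on any particular rate. The documents do not show that the investigators intend to draw that inference, and nothing here argues for a larger trial.

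**What to change.** Amend Clinical data analysis as follows.

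- Keep the planned counts and percentages, given as patients with at least one event in each arm.
- Add the risk difference between arms with a 95% confidence interval (Newcombe).
- Add an exact 95% upper limit for needling-related events and for serious events in the acupuncture arm, and say whether it comes from a two-sided interval (for 0/44, 8.0%).
- Treat any p-value for adverse events as descriptive, using Fisher's exact test where counts are sparse.
- State that a non-significant difference will not be taken as evidence of safety, and that any safety wording will rest on the interval and the upper limit.

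The cost is a few sentences and some table columns, with no added patients or data. The downside is a more modest safety statement. Recruitment is under way according to Progress of research, so the change should be made before results by arm are seen.
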